## Abstract

**Introduction and aim:**

Pakistan has a mixed-health system where up to 60% of health expenditures are out of pocket. Almost 80% of primary healthcare (PHC) facilities are in the private sector, which is deeply embedded within the country’s health system and may account for the unaffordability of healthcare. Since 2016, the existing national health insurance program or Sehat Sahulat Program (SSP), has provided invaluable coverage and financial protection to the millions of low-income families living in Pakistan by providing inpatient services at secondary and tertiary levels. However, a key gap is the non-inclusion of outpatient services at the PHC in the insurance scheme. This study aims to engage a private provider network of general practitioners in select union councils of Islamabad Capital Authority (ICT) of Pakistan to improve access, uptake, and satisfaction and reduce out-of-pocket expenditure on quality outpatient services at the PHC level, including family planning and reproductive health services.

**Methods and analysis:**

A 24-month research study is proposed with a 12-month intervention period using a mixed method, two-arm, prospective, quasi-experimental controlled before and after design with a sample of 863 beneficiary families from each study arm, i.e., intervention and control groups (*N* = 1726) will be selected through randomization at the selected beneficiary family/household level from four peri-urban Union Councils of ICT where no public sector PHC-level facility exists. All ethical considerations will be assured, along with quality assurance strategies. Quantitative pre/post surveys and third-party monitoring are proposed to measure the intervention outcomes. Qualitative inquiry with beneficiaries, general practitioners and policymakers will assess their knowledge and practices.

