### Study design

This research study will use a mixed method, two arms, prospective, quasi-experimental controlled before and after (CBA) design. The intervention group will include beneficiary families with existing in-patient coverage under SSP who will receive OPD services as part of the research study. In contrast, the control group includes families with existing inpatient coverage under SSP but will not receive OPD services.

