#### Study area

The study will be conducted in four (4) union councils (UCs) of ICT of Pakistan. Intervention and control arms will be assigned based on UCs selected for the study. The following are criteria for UC identification: (1) UC with sufficient residents of existing SSP beneficiaries, (2) UC in rural classified areas of ICT, (3) UC in which there is no public sector PHC level facility such as a Basic Health Unit (BHU), and presence of a network of private sector managed registered General Practitioners (GPs) providing primary healthcare services within identified UCs.

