#### Study population and sample size

The target population will be divided into (a) demand-side and (b) supply-side.

*Demand Side:* The total sample size for this study is 1726 beneficiary families (Baseline and end-line: control and intervention). This has been calculated by assuming the overall prevalence of health outcomes to be 50% (conventional) at baseline and an anticipated 10-percentage point change because of the intervention; with 80% power and 0.05 significance level, the total estimated sample was 388 for each study arm. The estimated sample was adjusted for a design effect 2 to account for facility-level clustering and 10% missing data / non-response. Hence an overall sample size of 863 families in the intervention- and 863 families in the control- group will be required to test the study objectives. Families in each study arm will be selected randomly from the available list of SSP beneficiary families from four peri-urban Union Councils of Islamabad Capital Territory (ICT). The intervention group (*N* = 863) will receive modified EPHS interventions as OPD services, while the Control group (*N* = 863) will not receive OPD services. Enrolled families in the intervention group will be informed about the project, and regular follow-up of SSP outpatient services accessed will be undertaken.

*Supply Side:* GPs who are members of Marie Stopes Pakistan’s primary healthcare franchise network will be selected based on their service provision status within the UCs identified for research study implementation. Individual and facility assessments will be done to ascertain the capacity to provide quality OP services to clients. A training curriculum will be jointly developed by the MoNHSRC, SSP, MSS, and WHO and will be used to train the selected GPs on the modified EPHS services. Periodic quality assurance visits and a centralized data-collection management information system will be implemented.

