### Quantitative household surveys

Before initiating the intervention, a household-based baseline survey is proposed that will cover not only the study population but also a subset of the general population from the same catchment who do not have the provision of any public or private sector health insurance. Findings will explore and explain health-related expenses and payment mechanisms if practiced or that exist other than the fee for service paid through OOP by clients in the study catchment area. The baseline survey will assess the prevalence of study indicators, document socio-economic and demographic information, out-of-pocket health expenditure, and document KAP regarding existing inpatient coverage and access and uptake of health services. A household-based endline survey at the end of 12 months of the intervention will help assess study outcomes – the impact of the outpatient services model on knowledge, attitude, and practice regarding health insurance, access, and uptake of outpatient services at the PHC level, user satisfaction, treatment outcomes, OOP health expenditure and financial protection.

Study participants for baseline and end-line assessment across the intervention and comparison arm will be selected randomly from the list frame of the SSP. Using quantitative and qualitative techniques, data collection methods will include a population-based household survey, providers’ assessment, and specific qualitative inquiry during the intervention, routine services, client satisfaction, and monitoring (clinical quality assessment) data will be done similarly to a previous study using the same design (50).

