### Possible limitations and strengths

Generally, quasi-experimental pre- and post-intervention designs are research methods that lack the random assignment of participants to groups, which is a characteristic of true experimental designs. But in our study, the beneficiary families in each study arm (intervention and control) will be selected randomly from the available list of Sehat Sahulat program beneficiary families from the four (4) peri-urban/rural Union Councils of Islamabad Capital Territory (ICT). However, the intervention and control of private-sector-owned primary healthcare facilities will be selected conveniently in the areas where similar primary healthcare public sector facilities are unavailable, and there is a scarcity of established private-sector PHC facilities. Nonetheless, the pre-post intervention design with control is internationally accredited when controlled experimental trials are not feasible due to logistic, financial, or other ethical reasons. While these designs have their strengths, they also come with limitations. Here are some considerations; for example, the quasi-experimental designs allow researchers to study interventions in natural settings. We will ensure no spillover within different intervention areas by choosing areas at a minimum distance from each other. The difference in cultural background of participants from the intervention and control areas can become a potential limitation. However, since the intervention and control areas are located within the same city, we believe the differences would be minimal and, consequently, have a limited impact on the study findings. Another potential limitation can be the presence of competing health providers providing similar primary health care services operating within the areas of project health providers. Selecting a similar healthcare facility for the project where no other service providers exist is difficult. To address this limitation, we will use the control group to assess the impact of routine practice in health facilities toward primary healthcare services, including family planning and sexual reproductive health services, anticipating that any increase in outcomes in our study will be due to the project intervention(s). We will conduct evaluation activities by hiring an external consultant and informing participants about the study’s purpose and confidentiality before collecting data. During regular monitoring from the research team, some random visits will be made to check the reliability of data.

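### The article calls random sampling of families randomization and offers it as the answer to missing random assignment, although arm follows union council and facilities are chosen by convenience

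*Protocol article*

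**What the plan says.** The abstract (Methods and analysis) states that 863 families per arm, 1726 in all, "will be selected through randomization at the selected beneficiary family/household level". The same sentence calls the study quasi-experimental, and Study design repeats the label: "quasi-experimental controlled before and after (CBA) design".

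The main text then describes how arms and families are obtained:

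- Study area: "The study will be conducted in four (4) union councils (UCs) of ICT of Pakistan", and "Intervention and control arms will be assigned based on UCs selected for the study".
- Study population and sample size: "Families in each study arm will be selected randomly from the available list of SSP beneficiary families".
- Quantitative household surveys: participants in both arms "will be selected randomly from the list frame of the SSP".
- Possible limitations and strengths: "the intervention and control of private-sector-owned primary healthcare facilities will be selected conveniently".

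The limitations section opens by granting that quasi-experimental pre-post designs generally lack random assignment, and replies: "But in our study, the beneficiary families in each study arm (intervention and control) will be selected randomly from the available list". It later says that the control group will be used in the expectation that any rise in outcomes is due to the project. Further on, it promises careful selection and justification of the control facility, a comparable control group, DiD analysis and covariate balance checks.

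**The concern.** Random sampling and random assignment answer different questions. Sampling decides which families from an area are measured. Assignment decides which families or areas receive the programme. Only the second gives a design-based reason to expect the arms to be alike apart from the intervention.

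The abstract's word belongs to the second idea, while the methods describe only the first. The limitations section goes beyond loose wording, because it puts the sampling forward as the reply to the absence of random assignment. It then attributes any increase to the intervention.

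The results are meant to support scale-up of outpatient cover through the national insurance programme. A reader who takes these statements at face value would give the effect estimate more protection from confounding than the design supplies.

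**Working it through.** **1. The stated sample size.** Inputs from Study population and sample size: 50% at baseline, a 10-point change, 80% power, significance level 0.05 (taken as two-sided), design effect 2, 10% non-response.

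n = [1.960 × √(2 × 0.55 × 0.45) + 0.842 × √(0.50 × 0.50 + 0.60 × 0.40)]² / 0.10²
= (1.379 + 0.589)² / 0.01 ≈ 387.3, rounded up to 388.

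388 × 2 = 776; 776 / 0.90 = 862.2, rounded up to 863; 863 × 2 = 1726.

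The article's figures reproduce exactly. The point concerns how arms are formed, so none of them changes.

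**2. What is random at each step.**

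| Step | Mechanism stated | Random? |
|---|---|---|
| Choice of union councils | Eligibility criteria (Study area) | No random mechanism stated |
| Arm of each union council | Based on the union councils selected (Study area) | No random mechanism stated |
| Facilities | Convenience (limitations) | No |
| Families within an arm | Draw from the programme list (sample size; household surveys) | Yes, as sampling |

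The only random step comes after arm is fixed. A family's arm follows from where it lives, and no family is described as being allocated to an arm by chance.

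**3. What the DiD removes and what it leaves.** For arm a, let L be the baseline level, S the change over the 12 months that would occur without the programme, and τ the programme effect.

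- Intervention arm: before L₁, after L₁ + S₁ + τ; change S₁ + τ.
- Control arm: before L₀, after L₀ + S₀; change S₀.
- DiD = (S₁ + τ) − S₀ = τ + (S₁ − S₀).

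The levels L₁ and L₀ cancel, so stable differences between areas are removed. The term S₁ − S₀ stays in full. Randomly sampling more families reduces the sampling error around τ + (S₁ − S₀); it does not move that quantity towards τ. Had families been assigned at random, S₁ − S₀ would be zero in expectation by design. Here it is zero only if parallel trends are assumed.

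The article says that the DiD accounts for pre-existing trends. The household surveys described are one baseline and one endline, and a single pre-intervention survey cannot show whether the areas were moving in parallel beforehand.

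**4. Scale.** The documents give no value for S₁ − S₀. Against the 10-point target, each percentage point of differential change is 1/10 = 10% of the target effect. This is a conversion factor and not an estimate of the bias.

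**5. The two accounts of facility selection.** The limitations section first says that intervention and control facilities are chosen by convenience, within areas lacking a comparable public facility. It later says that the control facility will be chosen with care so that the groups are comparable. Both could hold if convenience selection is restricted by comparability criteria, but the article does not say how the two fit together.

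**The case against.** The strongest reply is that nothing is concealed. The abstract's sentence carries the quasi-experimental label, and its disputed word describes how families are selected, not how arms are formed. The limitations section discloses convenience selection directly after the disputed sentence, concedes that validity is often compromised in such designs, and plans DiD and balance checks. Protection from selection bias is never claimed in so many words, and the detail of an adjustment model may properly sit in an analysis plan that is not shown.

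Most of this stands. It rules out reading the article as claiming to be a randomized trial, and it means that some control of bias exists. It does not rescue the reply in the limitations section: a correct label beside an argument that sampling makes up for missing assignment remains an inconsistency in the text itself.

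A reader might go further and infer two things that the documents do not support.

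- **That the effect is biased upward because the partner places the programme where its providers are strongest.** The article does not say so. Convenience selection applies to both arms, DiD removes stable differences in level, and a stronger site could start higher with less room to improve. The direction is unknown.
- **That drawing lots among the union councils would be an easy remedy.** Delivery relies on GPs in the implementing partner's own franchise, whereas the area criteria require only a network of registered private GPs. Focus groups with intervention families are planned during the baseline period, so arms appear to be known by then. The article also defends its design as one for settings where controlled trials are not feasible.

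**Conclusion.** The point holds in a limited form. The article attributes to the design a property it does not have: the abstract calls the selection of families randomization, and the limitations section treats random sampling as an answer to missing random assignment. The methods sections show that arm is set by union council without a stated random mechanism.

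Comparability of the arms therefore rests on parallel trends and on adjustment. Any differential change between the union councils enters the estimate one-for-one, in an unknown direction and of unknown size. The sample size is unaffected, and a larger sample would not help. The conclusion needs no assumption about how the four union councils are split between arms. It rests on reading the Study area section as describing non-random assignment, since no random mechanism is given there or elsewhere in the article.

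The correction should be made because it changes what the study may claim. It is not evidence that the result will be wrong.

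**What to change.** 1. **Abstract.** Replace the phrase on randomization at family level with *randomly sampled within non-randomly assigned union councils*.
2. **Limitations, reply to missing random assignment.** Delete the argument beginning "But in our study, the beneficiary families in each study arm (intervention and control) will be selected randomly from the available list". If the random draw is mentioned there, say that it supports representativeness of each arm's insured families and not comparability between arms.
3. **Limitations, attribution.** Soften the statement that any increase will be due to the intervention. Say that attribution depends on the union councils having had parallel change without it.
4. **Facility selection.** Reconcile convenience selection with careful selection of a comparable control: state which criteria restricted the choice and which part was convenience.
5. **Analysis.** Adjust the DiD for the socio-economic and demographic covariates that the baseline survey already collects. Where the same families are measured twice, let these covariates interact with survey period, because in a linear model on complete pairs a main effect alone leaves the DiD unchanged.

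Items 1 to 4 are wording. Item 5 needs no new data and only modest analysis time. Its limit should be stated: it addresses differential change linked to measured family characteristics, and it does not address changes peculiar to a union council or its facilities.

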**Conclusion and knowledge contribution:**

PHC should be the first point of contact for accessing health services and appears to serve as a programmatic engine for universal health coverage (UHC). The research aims to study a service delivery model which harnesses the private sector to deliver an essential package of health services as outpatient services under SSP, ultimately facilitating UHC. Findings will provide a blueprint referral system to reduce unnecessary hospital admissions and improve timely access to healthcare. A robust PHC system can improve population health, lower healthcare expenditure, strengthen the healthcare system, and ultimately make UHC a reality.

## Introduction

### Problem statement

Achieving Universal health coverage (UHC) is one of the overarching targets of the 2030 agenda for Sustainable Development Goals (SDGs). Target 3.8 of Goal 3 aims to “achieve universal health coverage, including financial risk protection, access to quality essential health care services, and access to safe, effective, quality, and affordable essential medicines and vaccines for all” (1, 2). UHC is about ensuring that people have access to the health care they need, when and where they need them without suffering financial hardship and includes the full range of essential health services, from health promotion to prevention, treatment, rehabilitation, and palliative care (3).

A Lancet study of 153 countries reports that universal health coverage improves access to essential care and advances the population’s health, significantly benefiting the poorest segment (4). Global commitment to UHC is reflected in the first-ever UN high-level meeting on UHC convened in September 2019 that reaffirmed the political commitment to UHC under point 10 of the declaration (5). Access to affordable, quality primary healthcare (PHC) is the cornerstone of UHC. A strong primary health care system is easy and convenient access to a trusted service provider or a team of providers that operates in the local community and seeks to address all health problems of the entire population (6). Thus, population health will improve by integrating primary care services with public health, lowering overall healthcare expenditure over time, improving the healthcare system’s performance, and ensuring improved equity provision and access for everyone (7). Available global evidence points to the success of social protection models and health financing tools such as insurance, conditional/unconditional cash transfers, vouchers, etc., in addressing inequities in access to primary, secondary, and tertiary care services to the underserved. These are reported to be an emerging high-impact best practice in maternal, neonatal and child health (MNCH) and family planning (FP) service delivery (8–14). However, there are disparities in access to and affordability of healthcare services, especially PHC services. At least half of the people globally do not receive these services, and high **out-of-pocket (OOP) expenses** push about 100 million people annually into extreme poverty (2, 15). Providing access to PHC services to lower socio-economic groups will increase the use of healthcare services (16, 17).

### Country context and rationale

With an estimated population of over 216 million, Pakistan is the fifth most populous country in the world, where 35% of the total population still live under the US$3.20 per day poverty threshold (18). Access to health care services is even more challenging for those living below the poverty line and residing in rural, hard-to-reach geographic areas. More than 80% of primary health care is in the private sector, deeply embedded in the country’s healthcare system, resulting in high OOP expenditure by service seekers (19). Most private health expenditures are out-of-pocket payments, as the percentage of current health expenditures stands under 60% (20). In some areas, most people bear these expenditures by selling their assets, borrowing from others, ignoring the problem, and remaining untreated (21). While health is delivered through public and private providers, the share of the private sector is significantly larger than the public sector. In Pakistan, the equitable UHC for essential health services, especially for maternal, newborn and child health services related to promotion, prevention, and treatment coverage among the general and the most disadvantaged population, stands at the lowest in the South Asian region (22). While the public sector funds over 30% of health expenditure in Pakistan, the private sector accounts for over 70%, amounting to more than 470 billion PKR (USD 2.1 billion) annually (19), with the majority, as described earlier, being OOP expenditures - 47% of the total expenditure is allocated to medications, while 29% is designated for outpatient care. In a given year, 7.65% of households experience catastrophic health expenses exceeding 10% of their total household spending (23). Therefore, at the individual level, this can be translated into every person in Pakistan paying on average $89 annually for seeking essential health care at the point of use, and this depriving household spending annually pushes 1% of the households in the country below the $1.90 a day poverty line (24).

A key objective of the UHC Partnership (UHC-P) is to develop a comprehensive set of essential healthcare services (25). Pakistan became part of the “Phase 3–2016-2018” UHC Partnership (UHC-P) in 2018. The activities conducted under this partnership include governance, financing, service delivery, health workforce development, and health information system enhancement. However, certain areas such as medicines, non-communicable diseases (NCDs), communicable diseases, maternal and child health, antimicrobial resistance, and health security are not covered. Despite UHC-P not primarily focused on primary healthcare (PHC), the 2018 country reports indicated that numerous activities supported by UHC-P aligned with the modernized PHC concept. For example, Pakistan expanded its benefits package to include maternal and child health, certain communicable and non-communicable diseases and multi-sectoral health interventions for PHC and higher-level facilities (25, 26). Universal Health Coverage (UHC) stands as a global priority. It constitutes target 3.8 of the Sustainable Development Goals (SDG), which aims to achieve “financial risk protection, access to quality essential health-care services, and access to safe, effective, quality, and affordable essential medicines and vaccines for all,” attaining this objective necessitates enhancements in both population-level interventions and individual health services to foster health promotion and deliver preventive and therapeutic care (27). Monitoring progress toward this target will be facilitated by indicator 3.8.1, which focuses on the coverage of essential health services, and indicator 3.8.2, which centres on financial risk protection (28). To enhance the effectiveness of UHC, researchers have proposed indices measuring the coverage of essential health services, aiming to optimize the outcomes of UHC initiatives (29, 30).

Researchers have made progress toward measuring universal health coverage (UHC), but far less is known about the utilization and unit cost of services of health systems that will expand coverage (31). Some studies provided evidence that even in settings where progress has been made on UHC, deaths due to poor quality services represent a substantial challenge (32). From a financing standpoint, underperforming health systems reduce the returns on UHC investments. However, when coupled with investments in health system quality, expanding insurance can result in major health gains, as shown by Thailand, Rwanda, and Costa Rica, which have pursued this dual strategy and achieved substantial improvements in survival in child and maternal health 28-30 (33–35). Similar improvements in reducing catastrophic health expenditure and another impact on the progress of UHC were seen in studies from Russia, Mexico and Myanmar (36–38).

The Government of Pakistan launched one of the largest social protection initiatives as early as 2008, entitled Benazir Income Support Program (BISP), which provided unconditional cash transfers every quarter to the poorest using a BISP poverty scorecard (39). In 2015–2016, the Ministry of National Health Services, Regulations and Coordination (MoNHSRC), Government of Pakistan, in collaboration with Provincial Governments, launched the Prime Minister’s National Health Insurance Program (later renamed as Sehat Sahulat Programme - SSP), representing a national effort to achieve UHC by covering the cost of treatment for insured families to access services for a range of preventive, curable and promotive healthcare services (40). SSP provides financial protection to millions of insured poor households by providing them with in-patient services at the secondary and tertiary levels (41, 42). The scheme currently covers more than 37 million families, and their beneficiaries get to avail these services at the approved empanelled facilities living in Islamabad, Punjab and Khyber Pakhtunkhwa (KP) provinces, Azad Jammu Kashmir (AJK) and Gilgit Baltistan (GB).

Globally, outpatient visits have increased by more than half, and inpatient admissions have increased by more than two-thirds since 1990. Still, from the effectiveness and efficiency viewpoint, more research is needed, especially in the local context, on the utilization and unit costs of primary health services in the health systems that will expand coverage over time (31). A key gap in the current Sehat Sahulat Program is the absence of coverage for Outpatient (or OPD) services at the PHC level - which includes services related to sexual and reproductive health, maternal and child health, family planning, neonatal care, nutrition, adolescent health, non-communicable diseases, and infectious diseases (43). To reduce OOP expenses for accessing PHC, a financial benefits package for outpatient services must be implemented within the Pakistani government’s SSP program.

